## Discussion

We present a novel data collection system that will support a prospective, non-blinded, non-randomized study to concurrently compare the performance of processed EEG indices from BIS and SedLine monitors. Although prior studies have demonstrated marginal correlation between the BIS and SedLine monitors with various anesthetic agents, these studies have been limited because they require non-standard sensor locations in order to apply both sensor arrays on the forehead of study subjects [22, 23]. Because not all sensors are positioned according to manufacturer’s instructions, the validity of prior comparisons is compromised. In addition, our inclusion of standardized clinical observations (acute changes in blood pressure or heart rate) in real-time and collection of raw and processed EEG waveforms will allow us to investigate the agreement of BIS and PSI indices across a wide range of anesthetic depth and establish correlations to clinical assessments and medication administration.

We recognize several limitations in our study design. Processed EEG indices may provide support for the clinical evaluation of anesthetic depth or disagree with clinical assessments during periods of arousal or deep anesthesia states. Therefore, a clinician’s decision to modify an anesthetic by administering additional volatile gas, opioid, or other medication may not always be in agreement with real-time brain function monitoring. Furthermore, changes in processed EEG indices may be delayed relative to cardiovascular parameters. Although the intraoperative anesthesia care team will be blinded to the processed EEG indices, the investigators are not blinded but will not report the processed EEG value to the anesthesia clinician at any point during the study. Our study design may be biased by the Hawthorne effect. The intraoperative anesthesia care team may behave differently while being watched by an investigator. In this setting, they may react to changes in blood pressure and heart rate differently when asked about these acute changes by the investigator and initiate interventions sooner or more frequently because of the observations. However, this observation is essential to capture the clinical assessment of possible “Deep Anesthesia Events” or “Arousal Events.” Although changes in cardiovascular parameters (heart rate and blood pressure) by 20% from the preoperative baseline may not always be clinically significant, redefining “Deep Anesthesia Events” and “Arousal Events” with greater absolute changes risks missing data points. Furthermore, this study is not randomized and has no control group. Data regarding associated outcomes such as postoperative delirium, PACU discharge time, accidental awareness, or recall will not be collected. However, this dataset may allow us to further investigate whether these measurable postoperative outcomes are linked to clinician and processed EEG disagreements regarding anesthesia depth, and could provide a focus for future investigation.

Our data may not be representative for all patient groups, particularly pediatric patients and those with severe systemic disease (ASA IV or V). Patients undergoing surgical procedures in the prone or lateral positions are also not represented given the variable contact between the EEG sensors and the patients’ forehead skin in these positions and the inability to reliably troubleshoot these problems. Additionally, interference from electrocautery limits our ability to reliably evaluate processed EEG indices in patients undergoing procedures of the head, neck, and face.

Real-time, simultaneous comparison of brain function monitoring devices using this electronic interface is the only way by which we can confidently and accurately investigate differences in proprietary algorithms. Our study design and custom engineered setup will allow a valid comparison of the BIS and PSI indices. Further research with our design will be necessary given the potential benefits of accurately assessing anesthetic depth.

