## Methods

### Study design and setting

This data collection system will be used in a prospective, non-randomized, non-blinded trial approved by the Institutional Review Board (IRB) at the University of California, Davis. The anesthesia providers responsible for the intraoperative care of included patients will be blinded to the processed EEG indices and not permitted to utilize these indices to guide the anesthetic management. Any adverse events observed throughout the trial will be communicated with the IRB and sponsor.

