### Data collection

Data collection will begin with a baseline set of BIS and PSI indices. Once recorded, general anesthesia will be induced with medications and doses chosen by the intraoperative anesthesia care team and documented in the electronic medical record (EMR). The depth of sedation during induction will be measured, at least, every minute using the Modified Observers’ Assessment of Alertness/Sedation (MOAAS) scale until the patient loses the eyelash reflex and achieves a score of 0. Two MOAAS scores can share the same timepoint if the patient achieves a new score less than 1 min from the prior score. The following descriptions of MOAAS scores will be used: 0 does not respond to pain; 1 does not respond to mild prodding or shaking; 2 responds after mild prodding or shaking; 3 responds after calling loudly or repeatedly; 4 responds slowly to voice with normal tone; 5 responds readily to voice with normal tone. Times indicating start of anesthesia induction, endotracheal intubation, surgical incision, and the start of electrocautery will also be recorded. Electronic, time-stamped documentation of intravenous medication doses in the EMR by the anesthesia provider will allow for retrospective review of their effects on raw and processed EEG data by investigators. Similarly, end-tidal concentrations of volatile gases will be automatically recorded in real-time within the patient’s EMR throughout the entire surgery.

Throughout the course of the surgical procedure, timepoints with acute changes of ±20% in blood pressure or heart rate from baseline values will be recorded. At these timepoints, an investigator will question the anesthesia provider regarding the suspected cause for each acute change as “Light Anesthesia”; “Deep Anesthesia”; “Volume Status”; or “Other.” The anesthesia provider will not be limited in responses for “Other.”

At the end of the surgical procedure, timepoints indicating incision closure, emergence from anesthesia, tracheal extubation, and return of consciousness will be recorded. During emergence, MOAAS will be measured every minute until the patient achieves a score greater than or equal to 4. Sensors will be removed prior to patient transport to the post-anesthesia care unit (PACU). A timeline of events and experimental recordings are shown in Fig. 4.

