**Fig. 4 Fig4:**
[figure not shown]
Timeline of Events and Experimental Recordings

Raw and processed EEG data will be organized according to the patient’s unique study identification number. Record of medication administration will be stored in the EMR and accessible to investigators by searching the patient’s medical record number (MRN). Preoperative patient demographics, vital signs, ethnicity, race, ASA status, description of surgical procedure, pre-existing diseases, surgical position, MOAAS scores, event timepoints, anesthesiologists’ assessments, and general comments will be written on the CRF, which will then be scanned, and electronically stored in a password-protected, encrypted N: drive.

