### Primary outcomes

This protocol’s primary endpoint is to establish the concordance, or extent of agreement, between the processed EEG indices from BIS and SedLine monitors and the real-time clinical assessments of anesthetic depth by clinicians during “Deep Anesthesia Events” and “Arousal Events.” Investigators will retrospectively review the EMR to identify interventions made by the anesthesia providers during 10 min surrounding (5 min before and after) periods of burst suppression noted on raw EEG or acute changes in blood pressure or heart rate ± 20% from baseline values. The performace of processed EEG indices surrounding periods of burst suppression on raw EEG will also be analyzed.

Clinically identified possible “Deep Anesthesia Events” are defined as acute decreases in blood pressure or heart rate greater than or equal to 20% from the patient’s preoperative baseline values. The clinical diagnosis of “Deep Anesthesia” coupled with any of the following on the raw EEG, BIS or SedLine monitors indicates agreement: burst suppression on raw EEG, processed EEG index value consistent with a deep anesthesia state per manufacturer recommendations (below 40 for BIS or below 30 for SedLine), or an acute decrease in the processed EEG index by 10 over the same index 5 min prior to the event. The actions of the anesthesia providers will also be examined during these timepoints, in particular the administration of hypnotic (such as propofol or volatile agent) or analgesic medication.

Clinically identified possible “Arousal Events” are defined as acute increases in blood pressure or heart rate greater than or equal to 20% from the patient’s preoperative baseline values. The clinical diagnosis of “Light Anesthesia” coupled with any of the following on the BIS or SedLine monitors indicates agreement: processed EEG index value that signifies inadequate anesthesia per manufacturer recommendations (greater than 60 for BIS or greater than 50 for SedLine), or an acute increase in processed EEG index by 10 over the same index 5 min prior to the event. The actions of the anesthesia providers will also be examined during these timepoints, in particular the administration of hypnotic (such as propofol or volatile agent) or analgesic medication.

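### Investigators who are not masked to BIS and PSI question the clinician at each event, event times are handwritten with no time window for an acute change, and no index-masked reader of burst suppression is described

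*Protocol article*

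**What the plan says.** Study design and setting: the anesthesia providers "will be blinded to the processed EEG indices and not permitted to utilize these indices to guide the anesthetic management".

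Discussion, limitations paragraph: "the investigators are not blinded but will not report the processed EEG value to the anesthesia clinician at any point during the study". The bias discussed next is the Hawthorne effect on the care team. Bias arising from the investigators' own knowledge of the indices is not mentioned.

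Data collection: "timepoints with acute changes of ±20% in blood pressure or heart rate from baseline values will be recorded", and at these times "an investigator will question the anesthesia provider regarding the suspected cause for each acute change". The answer is light anesthesia, deep anesthesia, volume status or other. The paragraph under Fig. 4 adds that "MOAAS scores, event timepoints, anesthesiologists’ assessments, and general comments will be written on the CRF", and that the form is then scanned.

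Primary outcomes: a deep-anesthesia rating agrees with the EEG if any one of three things is present: burst suppression on raw EEG, an index below the cut-off (40 for BIS, 30 for SedLine), or a fall of 10 in the index compared with 5 minutes before the event. A light-anesthesia rating agrees if the index is above the cut-off (60 or 50) or has risen by 10 over 5 minutes. There is no raw-EEG criterion for Arousal Events.

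Processed EEG setup: both sets of index data are recorded by software.

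**The concern.** The primary endpoint is agreement between a clinician's rating and the EEG at particular moments. It is cleanest when nobody who fixes the moment, asks for the rating or judges the waveform knows what the indices show. Here the clinician is masked, but the group that includes the questioner is not. The only stated safeguard is that the number is not spoken aloud.

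An investigator who has just watched an index move may ask at that moment, or ask in a different manner, without disclosing any value. A person who reads raw EEG beside a low index may be readier to call burst suppression. Either would make the two sides of the comparison less independent than the analysis assumes. Kappa corrects for chance agreement, not for this.

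**Working it through.** No figure in the document can be reproduced here: it gives no event count, expected agreement or target kappa. The check traces each route through the stated rules and then shows, on assumed inputs, why the effect cannot be signed.

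**Route 1, timing (Deep Anesthesia and Arousal Events).** The trigger is a 20% departure from the preoperative baseline, with no period over which the change must occur. If pressure stays more than 20% below baseline, many moments qualify. Suppose BIS stands at 50, falls to 40 and stays there.
- Event timed within 5 minutes after the fall: current value 40, value 5 minutes earlier 50, difference 50 − 40 = 10. The change criterion is met.
- Event timed later than that: current value 40, value 5 minutes earlier 40, difference 0. A value of 40 is not below 40, so neither index criterion is met.

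The same episode is classified differently according to the time written down. Software capture of the index does not prevent this, because the handwritten time decides which stored values are used.

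**Route 2, prompting.** The questioner belongs to the unmasked group, and the rating is taken live. The clinician does not see the index but can respond to when and how the question is put.

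**Route 3, burst suppression (Deep Anesthesia Events only).** This is the one EEG criterion that needs a reader's judgement, and it is sufficient by itself.

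**Illustration.** All inputs are assumed. Clinician-positive 40%, index-positive 30%, independent. Both-negative events are counted as agreement, as a kappa table needs; the article defines only the both-positive case.

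Cells: both positive 0.4 × 0.3 = 0.12; clinician only 0.28; index only 0.18; neither 0.6 × 0.7 = 0.42. Agreement = 0.12 + 0.42 = 54%. Chance agreement is also 54%, so kappa = 0.

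- *Logging depends on the index* (90% of index-positive moments logged, 70% of the rest). Index-positive share = 0.27/(0.27 + 0.49) = 35.5%. Agreement = 0.4 × 0.355 + 0.6 × 0.645 = 52.9%, a fall. Chance agreement equals this, so kappa stays 0.
- *Prompting moves 10% of discordant ratings to the index side.* Agreement = 0.54 + 0.10 × 0.46 = 58.6%. Clinician-positive share = 0.40 + 0.018 − 0.028 = 0.39. Chance = 0.39 × 0.3 + 0.61 × 0.7 = 54.4%. Kappa = (0.586 − 0.544)/(1 − 0.544) = 0.09.
- *Burst suppression is read into 10% of clinician-only events.* Agreement = 0.54 + 0.028 = 56.8%. EEG-positive share = 0.328. Chance = 0.4 × 0.328 + 0.6 × 0.672 = 53.4%. Kappa = (0.568 − 0.5344)/(1 − 0.5344) = 0.07.

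The first route lowers percent agreement and leaves kappa alone. The other two raise both, but only because the steering was assumed to run toward the index. The document fixes neither the rates nor the direction.

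**The case against.** The design is openly labelled non-blinded, and the limitations paragraph already says who is masked and who is not, so there is nothing to correct on that score. The clinician is blinded, the trigger is numeric and uses no index, a question is due at every acute change, and the index values are machine-recorded and judged against fixed cut-offs. All of this stands and limits the point.

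A reader might infer more, but the document does not support it:

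- *Investigators choose events by the index.* The person who records events is not named, and the rule is index-free. The room left is in the timing, because acute is undefined.
- *Investigators read burst suppression with the indices in view.* The article says only that it is noted on raw EEG. It does mention investigators' review of drug effects that "will allow for retrospective review of their effects on raw and processed EEG data by investigators", but this does not describe how burst suppression is scored. The full protocol, not shown, may name a masked reader.
- *Coding of interventions steers the agreement result.* It is true that "Investigators will retrospectively review the EMR to identify interventions made by the anesthesia providers", but interventions are examined alongside and do not enter the agreement rule.
- *Agreement must be inflated.* The rating is given after the moment is fixed, so an investigator could select on the index but not on concordance. As shown above, selection on the index alone need not raise agreement or kappa.
- *Sponsorship by the maker of one monitor shows bias.* It is disclosed and adds no mechanism.

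What remains is the explicit statement that investigators are not blinded, joined to their live role in obtaining the rating. The limitations text concedes that being asked may change the team's behaviour, but not that the asking may depend on the index.

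**Conclusion.** The point holds in a limited form. As written, the plan leaves three routes by which knowledge of BIS or PSI could influence the primary comparison: the recorded event time (Deep Anesthesia and Arousal Events), the prompting of a blinded clinician, and the reading of burst suppression (Deep Anesthesia Events only). The first rests partly on the inference that the unmasked investigator present also notes the times. The third rests on the absence of any described masked reader in a condensed article. The second is the most direct, since the article itself assigns the questioning to an investigator.

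The size and direction of any effect are unknown, and the illustrative figures describe no expected bias in this trial. The point is worth acting on because the remedy is inexpensive, not because the result has been shown to be wrong.

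**What to change.** 1. After the impedance and signal check, hide the BIS and PSI numbers from the investigator who times events and questions the clinician. Use one fixed, scripted question. No index data should be lost, since the values are recorded by software.
2. Set event times by a fixed rule, with a stated window for an acute change, applied to the recorded vital signs where an electronic record is available. Report the share of those events that were queried. The article describes electronic capture of drug doses and end-tidal gas but does not say this of blood pressure and heart rate, so availability must be confirmed.
3. Read burst suppression from raw EEG with the BIS and PSI values and the clinician's answer removed, including for patients already enrolled, whose raw EEG is stored.
4. Add to the limitations that unblinded investigators may bias event timing, questioning and burst-suppression reading.

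The cost is a small amount of data preparation and bedside troubleshooting that relies on the raw trace. Whether the displays can be hidden and the files exported without index values needs checking with the equipment in use. Recruitment is under way, so steps 1 and 2 should carry a start date, and results before and after it should be reported separately.

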### Trial status

This study is currently in the recruitment phase. Earlier publication of our study design was delayed so that the electrode sensors, custom-built passive interface box, and data collection system could be appropriately evaluated in clinical practice.

Sample recordings from 5 patients during general anesthesia induction utilizing our data collection system are shown in Fig. 5. Overall, BIS and PSI indices appear to change in parallel during general anesthesia induction. However, qualitative differences are apparent in studying these data.

**Fig. 5 Fig5:**
[figure not shown]
Changes in BIS and PSI indices during general anesthesia induction for 5 different patients

## Abbreviations

ASA: American Society of Anesthesiologists
ADC: Automated data collection
GND: BIS ground channel
BIS: Bispectral index
CRF: Case report form
CT: Common reference channel
ECG: Electrocardiogram
EEG: Electroencephalogram
EMG: Electromyography
EMR: Electronic Medical Record
CB: Ground channel
kohms: Kiloohms
LE: Left eye
LT: Left temple
MOAAS: Modified Observers’ Assessment of Alertness/Sedation
MRN: Medical Record Number
PSI: Patient state index
PACU: Post-anesthesia care unit
RE: Right eye
RT: Right temple
